#### Follow-Up Assessments and Outcome Measures

Upon completion of the baseline session, participants were reminded of the need to return for a follow-up assessment 3 months after the baseline session. The second study visit uses an Internet-based survey designed to assess the same behavioral and attitudinal domains captured through the baseline questionnaire. This allows us to evaluate any temporal changes in the frequency of substance use, injection risk behaviors, overdose risk, and HCV testing. The follow-up assessment also evaluates self-reported readiness to change, attitudes, and perceived norms, providing an opportunity to detect whether the tailored intervention may influence outcomes through these intermediate variables.

In addition to repeating the assessment of baseline variables for longitudinal analysis, the follow-up questionnaire captures information on participant perceptions about whether they met any of the health goals discussed in the baseline session. For participants determined to be HCV-infected at baseline, the survey assesses whether they received any follow-up testing or medical care for HCV since receiving their test result. Finally, it evaluates usability and acceptability of the intervention through a series of questions delivered to participants who were randomized to the active study arm. The additional questionnaire items used during the follow-up assessment are presented in Multimedia Appendix 3.

There are multiple behavioral outcomes of interest in this project. Accurate assessment of drug use behaviors may be limited because it relies on participant self-report and may be biased due to losses to follow-up. HCV testing behavior may be captured with greater validity because it will be ascertained by searching HCV testing data collected and reported by all agencies receiving funding from the Wisconsin Division of Public Health. For participants who have received a reactive HCV screening test result, we will determine whether any follow-up testing was performed, including confirmatory HCV RNA or HCV genotype tests, which would indicated that the participant was linked to evaluation and/or treatment of HCV.

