#### Sample Size and Power

Demonstrating efficacy of the intervention through detection of a statistically significant effect size was not a primary goal of the project. However, we considered it plausible that the intervention might significantly influence participants’ decisions to receive HCV testing even after a single session. While planning the pilot trial, we calculated a target sample size that would be sufficient to detect what we considered to be a meaningful difference in the proportion of participants who undergo HCV testing within 12 months after enrollment. Assuming that approximately 10% of participants would be known to have HCV infection at enrollment and accounting for expected losses to follow-up, we estimated that a sample size of 408 would provide 90% power to detect a difference of 0.15 in the proportion of participants who voluntarily returned for an HCV test within a year of enrollment.

We believed that achieving a target sample size of 408 was feasible and justified based on data from the pilot survey conducted in 2012 reporting that 69.4% of syringe exchange clients had an HCV test in the prior 12 months and 14.9% of clients had ever had a positive HCV test [1]. Because this intervention was targeting people who inject drugs but may not be regular users of the syringe exchange program, we anticipated that the number reporting prior HCV testing would be lower. We believed an effect size of this magnitude was reasonable based on prior meta-analyses of tailored communication interventions, which provide support for moderate mean intervention effect sizes [20] across a variety of health behaviors, including addiction-related behaviors (eg, smoking) and HIV risk-related behaviors [37]. Notably, findings suggested effect sizes increased with the number of behaviors intervened upon, with mean effect size of g=.24 (95% CI 0.18-0.31) for interventions focused on 3 behaviors [20].

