#### Data Analysis

Descriptive statistics reported here were calculated for baseline variables using SAS 9.3 (SAS Institute Inc). Differences in participant characteristics were assessed using a Wilcoxon rank-based general linear model approach for continuous variables and Pearson chi-square or Fisher exact tests for differences in categorical variables.

To evaluate the effectiveness of the risk reduction intervention, we will test within-group changes from baseline to follow-up (eg, change in frequency of needle-sharing) using the matched-pair Wilcoxon rank-sum test. Similarly, binary outcome changes will be examined using either the McNemar test or Fisher exact test.

To assess the independent role of the intervention in improving screening for HCV, we will use a logistic regression model on the binary outcome of having an HCV test within the 12-month period postintervention. Again, a Wilcoxon general linear model framework will be used for analysis of Likert scale outcome measures. Indicators pertaining to individual level outcomes within intervention and control groups will be measured among the same individuals at baseline and follow-up.

To avoid potential sampling bias toward individuals with larger networks, we will adjust regression models using inverse probability weights based on individual recruitment network sizes [33]. To account for correlation between recruiter and recruited, we will create a variable indicating who the recruiter of each subject was and use it as a cluster variable using generalized estimating equations. An exchangeable correlation structure within each cluster will be assumed (ie, correlation between any 2 subjects recruited by the same recruiter will be assumed to be the same). For all tests, a 2-sided *P* value of less than .05 is considered statistically significant.

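### The paired tests for self-reported behaviour use only people who return and make no randomised comparison, and no named step addresses the loss bias the article concedes

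*Protocol article*

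**What the plan says.** All of this is in the protocol article.

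- **Data Analysis, behaviour outcomes.** For effectiveness, "we will test within-group changes from baseline to follow-up (eg, change in frequency of needle-sharing) using the matched-pair Wilcoxon rank-sum test", and "binary outcome changes will be examined using either the McNemar test or Fisher exact test".
- **Data Analysis, attitude outcomes.** "a Wilcoxon general linear model framework will be used for analysis of Likert scale outcome measures"; whether the contrast is between or within arms is not spelled out.
- **Data Analysis, individuals.** Outcomes in both groups "will be measured among the same individuals at baseline and follow-up".
- **Data Analysis, corrections named.** "we will adjust regression models using inverse probability weights based on individual recruitment network sizes", plus generalized estimating equations with the recruiter as cluster.
- **Follow-Up Assessments and Outcome Measures.** Drug-use assessment relies on self-report and "may be biased due to losses to follow-up". HCV testing is contrasted as more valid because "it will be ascertained by searching HCV testing data collected and reported by all agencies receiving funding from the Wisconsin Division of Public Health".
- **Sample Size and Power.** The target was set "accounting for expected losses to follow-up", with no rate given.

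**The concern.** Two weaknesses meet in the behaviour analysis.

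First, a test of change within one arm is not a test of the intervention. Calendar time, regression to the mean and repeated questioning move both arms, and randomisation protects only a comparison between them.

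Second, the change is measured in returners. The article describes a population for whom return is difficult. Its Table 2 gives 68 + 56 = 124 of 234 (53%) homeless and 42 + 44 = 86 of 231 (37%) incarcerated in the past year, and its section on unanticipated challenges reports forgotten appointments, lack of transport and people who could not be reached by phone. If those whose behaviour worsened are less likely to come back, returners show an improvement that did not happen. The article admits that loss may bias these outcomes, yet every correction it names is aimed at something else.

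**Working it through.** **1. Which people each test can use.** The Wilcoxon test is called rank-sum but described as matched-pair, so I read it as the paired (signed-rank) test. It and McNemar need both values from each person. Fisher's exact test, the stated alternative for binary outcomes, is not paired, but its follow-up values still come only from returners. The network-size weights are stated for regression models, so they do not reach the paired tests, and they concern who was recruited rather than who returned. Recruiter clustering concerns correlation. None of these addresses loss.

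**2. Figure to reproduce.** There is none: no retention rate is stated. Every retention rate below is an assumption.

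**3. Within-arm change, same loss pattern in both arms.**

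Inputs:
- Past-3-month sharing at baseline is 71/234 = 30.3% (71 recent sharers; 234 people answered the sharing question).
- Assume no true net change: 10% of the arm stop sharing and 10% start.
- Assume 65% of those not sharing at follow-up return, and 50% of those sharing.

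| Group | Share of arm | Return | Returners, % of arm |
|---|---|---|---|
| Shares at both visits | 20.3% | 50% | 10.2 |
| Stops | 10.0% | 65% | 6.5 |
| Starts | 10.0% | 50% | 5.0 |
| Shares at neither | 59.7% | 65% | 38.8 |
| Total | 100% | | 60.4 |

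- Baseline sharing among returners: (10.17 + 6.5)/60.45 = 27.6%.
- Follow-up sharing among returners: (10.17 + 5.0)/60.45 = 25.1%.
- Apparent change: 1.5/60.45 = a fall of 2.5 points, where the truth is zero.

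If return depends instead on **baseline** sharing at the same rates, the discordant pairs swap (5.0% stop, 6.5% start) and the same arm shows a spurious **rise** of 2.5 points. The direction therefore cannot be assumed.

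In 126 controls the discordant pairs of the first case would be about 126 × 0.065 = 8 against 126 × 0.050 = 6. That imbalance would not reach significance by itself. It distorts the estimate and adds to whatever else is present.

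**4. Comparing the two arms' changes.** If both arms follow the first pattern, each shows a 2.5-point fall and the difference is 0. If 65% of controls return whatever their behaviour, control change is 0, the intervention arm shows a 2.5-point fall, and the spurious difference is 2.5 points.

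**5. Comparing follow-up levels between arms, no true effect.** Prevalence among returners = q·r_s / (q·r_s + (1 − q)·r_n), where r_s and r_n are the return rates of sharers and non-sharers at follow-up. Take q = 0.44 for illustration, from 71/161 among those who had ever shared.

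| Control r_n / r_s | Intervention r_n / r_s | Returners, control v intervention | Spurious difference |
|---|---|---|---|
| 70% / 50% | 70% / 50% | 35.9% v 35.9% | 0 (both about 8 points too low) |
| 80% / 80% | 85% / 75% | 44.0% v 40.9% | −3.1 points |
| 80% / 80% | 90% / 70% | 44.0% v 37.9% | −6.1 points |
| 60% / 60% | 70% / 50% | 44.0% v 35.9% | −8.1 points |
| 50% / 50% | 60% / 40% | 44.0% v 34.4% | −9.6 points |

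In the 60% row, overall retention is almost equal (60.0% v 61.2%), so similar retention totals would not rule the problem out.

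**The case against.** The best defence is that this is a condensed article about a pilot. Demonstrating efficacy was stated not to be a primary goal, and handling of missing data is commonly left to a full protocol or analysis plan not shown here. The article discloses the limitation, collects several means of contact, and takes HCV testing, the outcome behind its sample size, from a source that needs no return visit. Much of this stands. The absence of a missing-data section is not the point. The point is that the article does name its tests, names them for evaluating effectiveness, and those tests are exposed to a bias it admits.

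Four stronger readings are tempting, and the text does not support them:

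- **That a completers-only population is declared.** The sentence about the same individuals describes repeated measurement and does not say who is excluded. Restriction to returners follows from the paired tests; for the Likert model it is only suggested.
- **That bias is expected, for attitudes as well.** The article says drug-use assessment may be biased. It does not say this of attitudes.
- **That the planned behaviour tests yield a false arm difference.** They are within-arm and yield no arm difference. Distortion between arms arises only when someone compares the arms, and only if loss patterns differ.
- **That selective return on baseline behaviour alone proves a need for imputation.** Where return depends only on arm and baseline sharing, a baseline-adjusted comparison already removes that bias.

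**Conclusion.** The concern holds in a limited form. For self-reported behaviours, the article fixes tests that make no randomised comparison and rest on returners, while conceding possible loss bias that no named step addresses. If return depends on follow-up behaviour, within-arm change is biased even when loss is the same in both arms. Comparisons of arms are biased only when loss patterns differ by arm.

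The size is unknown because retention is not reported. Under the assumed patterns it is 2.5 points, in either direction, for within-arm change, and 0 to 9.6 points for follow-up levels compared between arms. These figures illustrate and do not estimate. A reader might infer that the trial's HCV-testing result is compromised too. It is not affected by this point, because it comes from agency records. The change is worth making, but nothing here shows that the results will be wrong.

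**What to change.** For survey outcomes, replace the within-arm tests with a between-arm model of the follow-up value adjusted for its baseline value, keeping the planned clustering by recruiter. Add multiple imputation, or inverse-probability-of-retention weights, built from arm, baseline risk variables (for example housing, incarceration, injection frequency and sharing) and the 12-month database test result. Report retention by arm and by baseline risk. Keep the returner-only analysis as a sensitivity analysis.

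The cost is modest analysis time, using baseline surveys held for all 235 participants and a database search already planned. Any model that uses the database result must wait for that search. Follow-up was still running when the article was written, so the change could be fixed before results were known.

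The drawback is reliance on data being missing at random given those variables. Return that depends on baseline risk is handled. Return that depends directly on follow-up behaviour, as in the first illustration, is corrected only so far as those variables predict that behaviour.

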#### Study Population, Recruitment, Eligibility, and Screening

Enrollment in the study began in September 2014, and all baseline assessments were completed by April 2015. Participants in the study were either clients of an established, multisite syringe exchange program operating in southern Wisconsin or peers recruited from the social networks of these clients. Eligibility criteria included age 18 years or older, injection drug use in the past 30 days, and willingness to provide contact information for the 3-month follow-up. Pregnant women and people who did not speak English were excluded. As one goal of the study is to conduct outreach among high-risk populations who do not regularly use prevention services, we used social network–based referrals to recruit the majority of the study sample. Syringe exchange clients were informed about the study and screened for eligibility during a routine encounter at the syringe exchange program. Upon completion of the baseline visit, study participants received referral coupons and were encouraged to refer eligible peers. Coupons were marked with a unique code number used to track referral chains. Participants received US $10 in cash as compensation for time spent completing the baseline study encounter and an additional US $10 for each eligible peer they referred (up to 5) who enrolled in the study.

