## Results

Between September 2014 and April 2015, 235 people completed the baseline survey. Baseline descriptive characteristics of the sample are displayed in Table 2. The racial/ethnic breakdown was reflective of the general population of the region, with non-Hispanic whites comprising 60.3% (129/232) of the sample and those self-described as black or African American comprising 28.1% (66/235). The median age was 35 years (range 18-63 years). While most participants who provided a valid address (131/219, 59.8%) lived in the city of Milwaukee, about one-third (70/219, 29.0%) of participants resided in a municipality with a population less than 50,000 residents, including 17.8% (39/219) who lived in a city with a population less than 5,000. Comparison of the control and intervention groups with respect to baseline characteristics demonstrated no statistically significant differences, assuming a 2-sided alpha of .05.

**Table 2 table2:** Baseline characteristics by intervention group (N=235).

Characteristics	Category	Control (N=126)	Intervention (N=109)
Age, years, median (IQR)		35 (28-46)	33 (27-44)
Gender, n (%)	Male	92 (73.0)	89 (81.7)
	Female	34 (27.0)	20 (18.3)
Race, n (%)	White	79 (63.0)	59 (54.1)
	Black	32 (25.0)	34 (31.2)
	Other or multiple	15 (12.0)	16 (14.7)
Ethnicity, n (%)	Non-Hispanic/Latino	112 (90.3)	102 (94.4)
	Hispanic/Latino	12 (9.7)	6 (5.6)
Highest education level, n (%)	Less than high school	17 (13.5)	7 (6.4)
	HS diploma or GED	61 (48.4)	51 (46.8)
	Some college or vocational school	45 (35.7)	47 (43.1)
	College degree	3 (2.4)	4 (3.7)
Currently employed, n (%)	No	92 (73.0)	69 (64.0)
	Yes	34 (27.0)	39 (36.0)
Legal income in last year, n (%)	None	31 (26.0)	30 (27.5)
	US $1-11,500	62 (51.0)	49 (45.0)
	More than US $11,500	28 (23.0)	30 (27.5)
Homeless during the past year, n (%)	No	58 (46.0)	52 (48.0)
	Yes	68 (54.0)	56 (52.0)
Incarcerated during the past year, n (%)	No	82 (66.0)	63 (59.0)
	Yes	42 (34.0)	44 (41.0)
Has health insurance, n (%)	No	20 (16.0)	11 (10.0)
	Yes	105 (84.0)	98 (90.0)
Has primary care provider, n (%)	No	53 (42.4)	39 (36.0)
	Yes	72 (57.6)	69 (64.0)

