Of the 235 participants who completed the baseline assessment, 80 (34.0%) agreed to receive a rapid HCV test, and 14 (17.5%) tests were reactive. The most common reasons given for declining the test were the participant had been previously tested (36/155, 23.2%), did not want to or did not feel ready to be tested (22/155, 14.2%), already knew he or she was HCV-positive (17/155, 11.0%), and did not have enough time (13/155, 8.0%).

Drug use characteristics of the baseline sample are displayed in Table 3. Heroin was the drug most frequently injected by participants and nearly half (105/235, 44.7%) reported that they inject on a daily basis. Most participants (161/234, 68.8%) reported they had shared syringes, cotton filters, or cookers with other people while injecting drugs in the past. Of those reporting sharing injection equipment in the past, 44.1% (71/161) had shared syringes, cottons, or cookers during the past 3 months, and 30.4% (49/161) reported they had never been tested for HCV.

**Table 3 table3:** Drug use characteristics by intervention group (N=235).

Characteristics	Category	Control (N=126) n (%)	Intervention (N=109) n (%)
Drugs injected in past 30 days	Heroin	111 (88.1)	92 (84.4)
	Prescription opioids	26 (20.6)	21 (19.3)
	Cocaine	36 (28.6)	35 (32.1)
	Methamphetamine	1 (0.8)	6 (5.5)
Frequency of drug injecting in past 30 days	Less than daily	67 (53.2)	63 (57.8)
	Every day	59 (46.8)	46 (42.2)
Has shared needles, cottons, or cookers	No	37 (29.6)	36 (33.0)
	Yes	88 (70.4)	73 (67.0)
Has had an opioid overdose	No	75 (60.5)	70 (64.2)
	Yes	49 (39.5)	39 (35.8)

Using social networks to recruit participants allowed us to reach a population that may have otherwise not been reached. In the first phase of the study, prevention staff recruited 40 individuals to participate who were existing clients of the syringe exchange program. These participants referred 195 peers who were determined to be eligible and were enrolled in the study. As shown in Figure 3, linking participants via referral chains allows visualization of 2 large networks and several smaller ones.

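### The GEE cluster variable groups people who share a recruiter, not recruiters with their recruits, so it does not deliver the adjustment the plan states; the randomised arm contrast is little affected, but overall rates and within-arm tests can be

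*Protocol article*

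**What the plan says.** All references are to the protocol article.

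- **Data Analysis, aim.** The clustering step is introduced with "To account for correlation between recruiter and recruited".
- **Data Analysis, method.** The analysts will "create a variable indicating who the recruiter of each subject was and use it as a cluster variable using generalized estimating equations". The exchangeable structure is then explained: "correlation between any 2 subjects recruited by the same recruiter will be assumed to be the same".
- **Data Analysis, other tests.** Effectiveness is also to be evaluated by within-group change from baseline, using a matched-pair Wilcoxon test and McNemar or Fisher tests. The network weights and the clustering are described afterwards, for the regression models.
- **Results, recruitment.** "Between September 2014 and April 2015, 235 people completed the baseline survey". Of these, "prevention staff recruited 40 individuals to participate who were existing clients of the syringe exchange program", and "These participants referred 195 peers who were determined to be eligible and were enrolled in the study".
- **Results, network.** The text on Figure 3 reports that "linking participants via referral chains allows visualization of 2 large networks and several smaller ones".
- **Study Population, Recruitment, Eligibility, and Screening.** Coupons went to study participants in general, coded so that chains can be traced. Payment was made "for each eligible peer they referred (up to 5) who enrolled in the study".
- **Randomization.** Allocation was simple and individual. Table 2 shows 126 control and 109 intervention participants.

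**The concern.** The aim concerns one kind of pair (recruiter with recruit) and the method another (two recruits of the same recruiter). A GEE treats people in different clusters as independent, so the correlation named in the aim is set to zero in the working model and is also missed by the robust variance. The variable also lacks an obvious value for participants who were not referred by a peer.

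At stake are the standard errors of whatever the regressions estimate besides the randomised contrast, such as overall testing rates and the coefficients of non-randomised covariates. The within-arm tests are also exposed, because randomisation protects a comparison between arms, not a change within one.

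**Working it through.** **1. Counts.** 40 + 195 = 235, which reproduces the enrolled total. Staff-recruited: 40/235 = 17.0%. Peer-recruited: 195/235 = 83.0%, so there are 195 recruiter-recruit pairs.

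**2. What the variable groups.** Let staff-recruited A recruit B and C, and let B recruit D. The recruiter codes are A: none; B: A; C: A; D: B. The clusters are {B, C} and {D}, with A undefined. The pairs A-B, A-C and B-D are all split; only B-C is modelled. Giving A his or her own code yields {A, B, C} and {D}, but B-D is still split, because B cannot carry both A's code and B's own. A single cluster variable keeps every recruiter with every recruit only if the cluster is the whole referral tree.

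**3. Is there more than one wave?** If the 40 had recruited all 195 directly, with five each as the limit (the article states five as the payment limit), no tree could exceed 1 + 5 = 6 people. That does not fit two large networks, and coupons were given to participants generally. Cross-wave links therefore exist.

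**4. Effect on the GEE.** A null simulation used 40 seeds and 195 recruits, at most five recruits each, several waves, individual 1:1 allocation, a 45% outcome rate, and an unweighted logistic GEE with exchangeable correlation (400 runs). The network shape and the recruiter-recruit correlations (0.3 and 0.6 on a latent normal scale) are assumptions; the largest chain averaged about 118 people. Monte Carlo error at 5% is sqrt(0.05 × 0.95/400) = 0.011.

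| Clustering | Arm-effect type I error, 0.3 | 0.6 |
|---|---|---|
| Recruiter code, seeds as singletons | 0.035 | 0.048 |
| Recruiter code, seeds dropped | 0.060 | 0.070 |
| Whole tree, uncorrected robust SE | 0.135 | 0.150 |

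- Arm effect, recruiter code with singleton seeds, at 0.6: mean SE 0.257 against an empirical SD of 0.254.
- Intercept (overall rate), same setting: mean SE 0.194 against an empirical SD of 0.283. The ratio is 0.194/0.283 = 0.69, so the SE is 31% too small. A nominal 5% Wald test would then reject about 2 × [1 − Φ(1.96 × 0.69)] ≈ 18% of the time.
- Whole tree, at 0.3: mean SE 0.208 against an empirical SD of 0.256.

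Some fits failed to converge in some settings, including whole tree at 0.6, so that 0.150 is approximate. A further set of simulations gave the same pattern: arm contrast 0.035 to 0.058 with recruiter-code clusters and singleton seeds, overall-rate tests 0.07 to 0.51, whole-tree arm contrast 0.10 to 0.13, and a re-randomisation test 0.035 to 0.060.

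**5. Within-arm paired tests.** Type I error at nominal 5%, from simulations of 2,000 to 3,000 runs. Ranges show repeated runs. Tree sizes and correlations are assumed.

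| Assumed structure | 0.05 | 0.10 | 0.20 |
|---|---|---|---|
| Two trees of 70, 38 of 2-3; same correlation throughout a tree | 16-19% | 25-26% | 38-40% |
| Two trees of 40, the rest small; same correlation throughout a tree | 9-10% | 13-14% | 21-22% |
| 40 near-equal trees; same correlation throughout a tree | 6% | 9% | 11% |
| Two trees of 70; correlation decaying along referral links | 4.9% | 5.3% | 7.9% |

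**6. If the 40 were dropped.** The SE would rise by sqrt(235/195) = 1.098, about 10%. Power for a 0.15 difference, with no other loss, would fall from 0.734 to 0.652 (control rate 0.20), 0.644 to 0.564 (0.50) or 0.782 to 0.703 (0.694), about 8 points each time. The control rates are assumed, as the sample-size section states none. If the 40 are kept, nothing is lost.

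**The case against.** The strongest reply is that the one comparison that matters is safe. Allocation was individual within chains, recruiter-code clustering left the arm test near nominal, and the article says that demonstrating efficacy was not a primary goal. This stands for the randomised contrast, provided the seeds are kept and there is no spillover between recruiter and recruit. It does not cover overall rates, non-randomised coefficients or the within-arm tests.

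A second reply is that coding an identifier is a detail for the full plan. That is fair for the 40 seeds: they could be singletons, carry their own code or be coded to staff. It does not remove the mismatch, because the article itself explains the modelled correlation as that between co-recruits.

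Three stronger readings are tempting and are not supported:

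- *Network dependence is ignored altogether.* It is not; co-recruit correlation is modelled.
- *17% of the sample will be lost.* No text excludes the seeds; loss is only one possible coding.
- *The trial's type I error is as high as 38-40%.* That figure belongs to the within-arm tests, not the GEE, and to one assumed structure. Figure 3 is not shown, and no tree sizes or intraclass correlations are given.

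**Conclusion.** The concern holds as a mismatch between a stated aim and the method chosen for it. As worded, recruiter-recruit and cross-wave correlation is omitted for up to 195 pairs. The exact number depends on how the seeds are coded.

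The consequences are uneven. The arm contrast is near nominal with seeds retained. The SE for the overall rate was about 31% too small under a strong assumed link correlation. Inflation in the within-arm tests runs from about none (weak correlation decaying along links) to about 40% (strong tree-level correlation with two dominant trees). These sizes rest on assumed network shapes and correlations, and the GEE simulation did not include the planned inverse probability weights. The mismatch itself needs no assumption beyond the article's wording. It is worth correcting before the outcome analysis, but it does not threaten the randomised comparison.

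**What to change.** 1. **Reconcile aim and cluster definition**, using the chains recorded by the coupon codes. Either state that only co-recruit correlation is modelled, or adopt a dependence model that includes recruiter-recruit and cross-wave links.
2. **State that all 40 staff-recruited participants are retained**, and how they are coded, for example as singleton clusters.
3. **Take the arm-effect P value from a re-randomisation test** that reproduces the simple individual allocation. It is valid under the sharp null of no effect and no spillover, whatever the network correlation.
4. **Do not rely on uncorrected whole-tree robust standard errors.** Two trees dominate, and the simulated arm test then rejected too often. If trees are used as clusters, a small-sample correction is needed, and its performance with two dominant trees should be checked first.
5. **Base effectiveness conclusions on the randomised between-arm comparison**, and label the within-arm tests as descriptive.

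An analysis by the recruiter's arm, as a check for spillover, is optional and would have low power.

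The cost is a few sentences in the analysis plan and a re-randomisation script. No new data are needed, since the coupon codes already trace the chains.
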